### Risk factors for overdoses

Recent non-fatal overdose has been shown to represent a marker for increased risk of subsequent fatal overdose [18–20]. Recent period of abstinence, such as post-release from prison [21–24] or inpatient treatment [25–27], polydrug use [28–32], are risk factors highly associated with opioid overdose. Retention in opioid substitution treatment (OST) is associated with reduction of mortality and morbidity [33–39]. However, the OST population in Europe is ageing, with a mean age of death (39.4 years) increasing steadily [1], and carries a high degree of burden when it comes to chronic disease and multi-morbidity [29, 40] which also adds to the risks of overdose. Contrary to many beliefs, tolerant older users have been shown to have a higher risk of death due to overdose than novice users [28, 41].

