#### Methods

All NEPs (4, in the cities of Malmö, Lund, Helsingborg and Kristianstad) and OST clinics (18, in the cities of Malmö, Lund, Helsingborg, Kristianstad, Ystad, Ängelholm, Landskrona and Trelleborg) in the region were included in the project and in the research study, conducted by Lund University. Attempting to reach the population of individuals who have chosen not to visit NEP or enrol in OST, the project also included the emergency ward and the opioid detox ward at Malmö Addiction Centre, serving a majority of the population in Skåne. The goal is to offer OPEND to all individuals visiting targeted units, and to include 2000 individuals in the study. In the present setting, as from hospital records, NEP participants can be identified from their unique personal identification numbers, as NEP participation and interventions by NEP staff are documented. This enables systematic and longitudinal research including NEP patients in the present setting, including follow-up of NEP attendance over time. Several previous research studies from the present setting have originating from the identification of patients attending NEP units in the region [42, 84–86].

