### Statistical methods

Comparison of mortality, before and after intervention, is done by Poisson regression with an indicator variable for the intervention (0 = comparison, 1 = intervention), adjusting for age and gender distribution. The effect is described as RR (relative risk), with 95% confidence intervals. *P* values < 0.05 will be considered as statistically significant. The primary outcome measure relates to mortality in the overall cohort. The effect on mortality will be studied in OST and NEP separately, using a subgroup analysis. The evidence in effect between the cohorts will be described by the *p*-value of an interaction test. Outcomes are studied year by year during the intervention period, compared to the comparison period, year by year.

For the study aims regarding the included cohort, this is open, dynamic cohort based on individuals in OST and NEP, where they contribute with person time, as at-risk from entry to study end or death, or by possible exit from the cohort (the earliest of these three events is the end date of the personal time calculation). In the general population analyses, 2013 to 2017 constitute the comparison period, while corresponding data, during 2019–2023, constitutes the intervention period.

Each person included in the follow-up will contribute a record (row) in the research database for each year this person is included in one of the two cohorts. In the row, in addition to each individual’s consecutive number, variables such as date, sex, age, cohort (1 = OST, 2 = NEP), intervention (0 = comparison, 1 = intervention), person time, date in the event of death, and status (alive/dead) at the end of each year, will be registered. In addition, based on public registers of the number of patients in OST, in the analyses it will be possible to control for fluctuations in OST availability (number of patients in methadone and buprenorphine treatment, respectively) in the region, as OST availability is likely to affect mortality rates; for example, based on national register data from the present setting, it has been shown that the risk of overdose mortality varies depending on OST status [90].

Significance, as above, is 5%, when applying a double-sided test. The target for the statistical strength is set at 80% for primary outcome. Secondary outcome and subgroup analyses have not been calculated in strength.

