#### Recruitment

Recruitment began in June 2018 and will end in June 2021. On completion of the training session, patients are asked if they are interested in participating in the study. The trainer provides the patient with written and oral information about the study and how patient confidentiality will be protected. The trainer should also be able to answer questions raised by participants. If not, the project leaders are to be contacted without delay. Interested patients will then provide a written informed consent where upon they will be asked to fill in baseline questionnaire. Individuals declining study participation will access the same OPEND model as the individuals entering the study, and no compensation is given to the study subjects. The informed consent provided by included patients in the cohort study includes the follow-up in register data (national patient register and regional hospital and ambulance registers) for a three-year period, and register follow-up is carried out during the full three-year period, unless the patients contacts the researchers in order to withdraw consent. In case a patient ceases to show up in OST or NEP facilities in the region, only the self-report data regarding witnessed overdoses and naloxone administration will be dropped from further data collection.

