### Data analysis

#### Data storage and missing data

Collected data from active intervention participants are registered in an electronic Case Report Form (e-CRF). A unique e-CRF is created for each active participant, separated from the identification of the study participant, and stored in the clinical trial software RedCap. Data are stored confidentially and cannot be accessed by anybody outside the study staff. All questions in the e-CRF are to be answered actively, if questions are not replied to, they shall be marked as NA = “Not applicable” or NK = “Not known”.

During the first 5 months data was collected on paper, as the use of the computerized application was delayed. In November 2018, each unit received their own iPad, which was provided for by the project, containing the RedCap application. Patient information and consent is still provided on paper. The 5 months of data collected on paper will be entered in the e-CRF by a research administrator at Lund University.

There will be no registration of individuals declining naloxone training. During the 3 years that the project will be running, individuals could have visited many of the sites, and have, most likely been asked on several occasions. However, aggregated data from OST and NEP facilities in the region will enable descriptions of whether included participants differ from these overall populations on a group level.

Statistical data are drawn from available data registers. Each individual included by follow up will contribute to the research database with one entry (row) for each year, in either cohort. During the follow up period, person-time time after cohort regression, will not be taken into account.

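### Two follow-up rules for mortality in included patients conflict: person-time stops on leaving OST/NEP in one place, while register follow-up runs the full three years in another

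*Protocol article*

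**What the plan says.** Secondary outcome measures in included patients lists all-cause mortality and overdose mortality, each with a 3-year time frame. Other sections of the protocol article then give two accounts of how long a participant is followed for these outcomes.

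**Stop at exit.** For the aims on included participants, Statistical methods says "this is open, dynamic cohort based on individuals in OST and NEP". Time at risk ends at study end, at death, "or by possible exit from the cohort (the earliest of these three events is the end date of the personal time calculation". The database holds a row "for each year this person is included in one of the two cohorts", coded 1 for OST and 2 for NEP. Data storage and missing data adds that "person-time time after cohort regression, will not be taken into account".

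**Carry on.** Recruitment says that "register follow-up is carried out during the full three-year period, unless the patients contacts the researchers in order to withdraw consent". If a patient no longer shows up at OST or NEP, "only the self-report data regarding witnessed overdoses and naloxone administration will be dropped from further data collection". Quantitative data collection gives 36 months of follow-up for the cohort-specific analyses.

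**Risk in and out of care.** Risk factors for overdoses states that "Retention in opioid substitution treatment (OST) is associated with reduction of mortality and morbidity". Statistical methods adds that the risk of overdose death depends on OST status.

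**Who is recruited.** To reach people outside NEP and OST, Methods says that "the project also included the emergency ward and the opioid detox ward at Malmö Addiction Centre".

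**The concern.** The two rules give different death counts and different denominators from the same register data. Take a participant who leaves OST at month 12 and dies of an overdose at month 20. The death belongs in the 3-year outcome under Recruitment and Quantitative data collection. It is excluded under Statistical methods and Data storage and missing data.

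The choice matters because leaving care is not neutral with respect to death. If mortality is higher out of OST than in it, a rule that discards time out of care discards proportionally more deaths than person-years. The resulting rate lies below the 3-year mortality that the outcome names. The planned adjustment for age and gender does not correct this. While both rules stand, the choice between them could also be made after the deaths are known.

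There is a smaller coding gap. A participant recruited on a ward who is in neither OST nor NEP has no code in the two-level cohort variable, and so no defined exit. A participant in both has no single code.

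**Working it through.** **1. What the plan's own figures cover.** The stated powers (81%, 81% and 57% for 8000 against 3000 person-years, two-sided 5%) reproduce as 80.6%, 80.4% and 57.0% with a pooled-variance two-proportion calculation. They are not in dispute. They take a constant 2000 people and say nothing about exit.

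**2. The two rules side by side.**

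| Event within 36 months of inclusion | Statistical methods; Data storage and missing data | Recruitment; Quantitative data collection |
|---|---|---|
| Death while in OST or NEP | counted | counted |
| Move from OST to NEP, then death | counted (still in one of the two cohorts) | counted |
| Leaves both, then death in the register | not counted | counted |
| Withdraws consent | follow-up ends | follow-up ends |

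Only the third row differs, and the protocol gives reason to expect raised risk there for people leaving OST.

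**3. Size, with assumed inputs.** Let *f* be the share of 36-month person-time after exit and *k* the ratio of mortality after exit to mortality in care. The documents give neither, so both are assumptions. With in-care rate *r*:

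- full-follow-up rate = r × [(1 − f) + f·k]
- rate reported under stop-at-exit = r
- share of deaths dropped = f·k / [(1 − f) + f·k]
- reported rate ÷ full rate = 1 / [(1 − f) + f·k]

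Each cell shows share of deaths dropped / reported rate as a fraction of the full rate:

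| f | k = 1 | k = 2 | k = 3 | k = 4 |
|---|---|---|---|---|
| 10% | 10% / 1.00 | 18% / 0.91 | 25% / 0.83 | 31% / 0.77 |
| 20% | 20% / 1.00 | 33% / 0.83 | 43% / 0.71 | 50% / 0.625 |
| 30% | 30% / 1.00 | 46% / 0.77 | 56% / 0.625 | 63% / 0.53 |
| 40% | 40% / 1.00 | 57% / 0.71 | 67% / 0.56 | 73% / 0.45 |

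At k = 1 deaths are lost but the rate is not biased.

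**4. In counts.** The planned 2000 participants over 3 years give at most 6000 person-years. Take 30 per 1000 as the in-care rate (the lower baseline in Power and sample size, used here only as an illustration), f = 20% and k = 2.

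- In care: 4800 × 0.030 = 144 deaths.
- After exit: 1200 × 0.060 = 72 deaths.
- Full follow-up: 216 deaths in 6000 person-years, or 36 per 1000.
- Stop at exit: 144 deaths in 4800 person-years, or 30 per 1000.

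**5. Effect on a before-after ratio.** Write m = (1 − f) + f·k, with m₀ for the comparison period and m₁ for the intervention period. Each reported rate is the full rate divided by its m, so reported RR = full-follow-up RR × m₀/m₁. If exit and post-exit risk are the same in both periods, m₀ = m₁ and the RR is unchanged. The OST/NEP interaction is unchanged if m₀/m₁ is the same in the two groups.

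**The case against.** The strongest reply is that the two passages do different jobs. Recruitment governs which data continue to be collected. Statistical methods governs time at risk in an open cohort, where ending time at exit is a recognised design and in-care mortality is a legitimate quantity. Exit is also not defined, and a condensed article may leave the definition to a fuller document. This softens the conflict but does not remove it. In-care mortality is not the 3-year mortality of included patients that the outcome list names. The cohort definition, the yearly rows and the sentence on disregarded person-time all point to exit meaning leaving OST/NEP. If withdrawal or emigration was meant, the text still needs to say so.

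Four stronger readings are tempting, and the documents do not support them.

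- **The primary outcome is distorted.** Primary outcome measures defines it as opioid-intoxication deaths in the general population from national registries, to which no exit rule applies. Statistical methods does tie the primary outcome to an overall cohort, but that is a separate inconsistency.
- **The discarded time is the highest-risk time.** The documents give a direction for OST only, without a rate ratio, and say nothing about risk after leaving NEP, where about half the planned participants are to be recruited. Their remark on recent abstinence names prison release and inpatient treatment, not leaving OST or NEP.
- **The before-after RR and the interaction are biased.** They would be only if exit patterns or post-exit risk differ by period or cohort, and nothing in the text shows that.
- **No ward recruit has a cohort code.** Power and sample size describes naloxone recipients as NEP or OST clients, so some ward recruits may well have one. The gap concerns those in neither.

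Two further points stand. A 36-month clock from inclusion cannot be applied to comparison-period people, who were never enrolled. And the consent wording in Recruitment names the national patient register and the regional hospital and ambulance registers but not the cause-of-death register, so coverage for mortality should be confirmed.

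**Conclusion.** The concern holds for the secondary outcomes of all-cause and overdose mortality in included patients. The article gives two incompatible follow-up rules, and the one in the analysis section is likely to understate 3-year mortality because, by the protocol's own account, mortality is related to OST retention and status.

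The size cannot be determined from the documents. Over the assumed range (10–40% of person-time after exit, mortality ratio 1–4), 10–73% of deaths are dropped and the reported rate is 1.0 to 0.45 times the full-follow-up rate. The conclusion assumes that exit means leaving OST/NEP, which is the likeliest reading but an inference. The direction of the bias requires a mortality ratio above 1, which the text supports for OST and leaves open for NEP. Any effect on the before-after RR or the OST/NEP interaction is conditional, as shown in step 5 of the working.

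**What to change.** - For included participants, end person-time at the first of death, emigration, withdrawal of consent or 36 months after inclusion, regardless of attendance. Amend Statistical methods and Data storage and missing data to agree with the outcome list, Recruitment and Quantitative data collection.
- Report the in-care-only analysis as a labelled sensitivity analysis, with exit from OST and from NEP defined. OST/NEP status may be added as a time-varying covariate in a secondary model.
- For any before-after cohort comparison, specify one entry and exit rule that can be applied identically in both periods, since comparison-period people have no enrolment date.
- Add cohort codes for ward recruits in neither OST nor NEP and for people in both.
- Settle this before deaths are linked, and confirm that the consent covers the cause-of-death data.

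The cost is wording and database coding, because three-year register follow-up is already planned. The downside is that some of the person-time will come from people who no longer carry naloxone. The in-care sensitivity analysis addresses this in part.

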### Structure of implementation – the cascade model

Based on the training curriculums developed by the Harm Reduction Coalition [91], and in accordance with WHO guidelines (2014) [92], the naloxone education was developed by Practicum Clinical Skills Centre Malmö, in collaboration with the naloxone project leaders and by the guidance of the Danish Naloxone project RedLiv [79]. Participants from the User’s union in Skåne, the head of each unit and a key trainer, appointed by each unit, were represented at the naloxone workshop, November 2017. The session provided participants with the opportunity to receive information about the naloxone project and exchange opinions on the material and model of implementation. Before project start, an open information session about the naloxone project, was held, targeting members of the public and collaborators, such as social services, police and low threshold shelters.

The information material and material used in training curriculums was approved by the User’s union, Skåne, and by co-workers on various levels of the organisation, before the key-trainer sessions were held in 27th of March and 19th of April 2018. The compulsory three-hour training curriculums were held in Malmö, the largest town in the region. An extra key-trainer session was held at the NEP in Kristianstad. Each unit also received a CPR-dummy enabling practicing steps in education requiring practical exercise. The CPR-dummy had a replaceable face and lungs to ensure hygienic demands and to facilitate practical education when done in groups. The education material was sent to all key trainers, providing them with easy access material, with the purpose of key trainers educating their peers before project launch.

After initial training, before launching the project on the 11th of June 2018, all participating units were sent a link to an on-line booking site where the project leaders could be booked for on-site assistance during the first trainer-patient session.

Information and educational material for key trainers, staff, patients and their family and friends, who might benefit from OPEND, were provided by project leaders before launch at each unit. The project also provided the units with as many naloxone kits as each unit requested. The naloxone-kit - a small red bag, contains vinyl gloves, breathing mask, wipes, leaflet with “easy-to-use” instructions, a certificate for trainer/patient to sign after completing training session and a card with informing the overdose victim that they had received treatment with naloxone. The naloxone itself had to be requisitioned through the same system where all other medication is requisitioned, at the expense of the naloxone project. Every kit contains two single naloxone sprays, each dose delivering 1.8 mg naloxone as hydrochloride dehydrate.

OPEND training (Fig. 1) for users comprises a theoretical and a practical section. The theoretical section contains information on opioid receptors and effects of naloxone, risk factors and their possible impact on opioid overdose, how to identify and how to respond to an opioid overdose (is the person conscious/ breathing, call for ambulance, administer naloxone, airway management, recovery position, stay and observe consciousness and breathing). These steps are repeated as participants then practice on CPR dummy. Training lasts for 5–15 min, depending on trainee’s prior experiences and training. Sessions are held in groups or individually and can be extended if trainees request additional information or practical training to know more.

**Fig. 1 Fig1:**
[figure not shown]
Training model OPEND Skåne Region – flowchart

New staff are educated by key trainers, however project leaders are available for extra training sessions for staff and for key trainers. Open access information and education material is available on-line. Training can be provided by any member of staff who has completed the trainer education. Until November 2018, naloxone had to be prescribed by a physician, but can there-after be prescribed by a registered nurse. The naloxone kit is free of charge, and is provided to the trainee directly after training.

### Sample

#### Patient eligibility

First priority was to recruit patients from targeted units including 18 OST units, four NEPs and one emergency addiction unit and one in-patient detox ward for opioid dependence, serving under Addiction Center Malmö. Additional units will be eligible for inclusion when the project is implemented in prioritized units. Patients are eligible for the cohort study if they are 18 years and older, currently treated at the Addiction centres, or listed at NEP of Skåne County and have signed an informed consent. Exclusion criteria are restricted to subjects unable to understand study information due to psychiatric co-morbidity or severe language difficulties.

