#### Power and sample size

Power has been calculated only for the primary outcome measure. The total population at risk of fatal overdose in the general population is unknown, as people may be at risk of overdose death either because of a severe opioid dependence, a less severe state of dependence or a more unregular use of opioids. As the number of potentially affected individuals is unknown, the power calculations were based on numbers calculated from the number of individuals reached by the intervention at NEP and OST facilities. Thus, power calculations based on the cohort planned to receive distributed naloxone will be considered to be a minimum level with the possibility of a higher effect if the naloxone intervention disseminates also beyond the NEP and OST populations.

The number of patients in OST and NEP is estimated to comprise approximately 2000 individuals, 1000 individuals respectively. Power was calculated based on potential mortality in these two groups (calculated conservatively for 4 years prior to the intervention); a total of 4 × 2000 = 8000 person years; referred to as a ‘comparison period’), and with the conservative assumption that the intervention is calculated to reach the full study group for 1.5 years (intervention group, 2019–2020) (1.5 × 2000 = 3000 person years). The statistical power calculations are made with the Microsoft Excel sheet EPISHEET available for download at www.krothman.org/episheet.xls (downloaded on 14 January 2016).

Assuming that mortality before intervention is 50 deaths per 1000 person years in the overall cohort (that is, a 5% annual risk), a relative risk reduction of 25% (relative risk RR = 0.75) is required in order for the statistical strength to exceed 80% (81%), 5% significance limit, two-sided test, with 8000 person years before intervention (comparison period) and 3000 person years after intervention (intervention group). If however, assuming that mortality before intervention is 30 per 1000 person years in the overall cohort (that is, a 3% annual risk), a higher relative risk reduction, 32% (RR = 0.68), is required for the statistical strength to exceed 80% (81%), 5% significance limit, two-sided test, with 8000 person years before intervention (comparison period) and 3000 person years after intervention (intervention group). If the risk reduction still is 25%, even in this scenario, the statistical strength drops to 57%.

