### Trial status

In July 2018, 3 weeks into the project, 70% of targeted units (*N* = 24) were included, providing OPEND and including subjects into the study. Five weeks into the project 87% of targeted units had started, after 12 weeks, all units were including patients in the project. After inclusion and establishment of the first targeted 24 units, making sure the program is well established into daily management, the naloxone project has recently included another 3 units, and are planning on further expansion. So far, reports from included units are indicating that upon completion of training, approximately 80% of patients are giving their consent to study inclusion. The intervention period begins 1 July 2019 (with the first analyses conducted for general population data for the 18-month period of 1 July 2019–31 December 2020), based on the assumption that the naloxone distribution will be considered to have reached a satisfactory level from July 2019.

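### The before/after OST/NEP mortality comparison has no entry rule for its comparison rows, and the only cohort rule stated, consent after training, cannot apply to them

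*Protocol article*

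**What the plan says.** **Analysis.** Statistical methods plans "Poisson regression with an indicator variable for the intervention (0 = comparison, 1 = intervention), adjusting for age and gender distribution". Each person contributes one row per year in the OST or NEP cohort, and each row carries the 0/1 intervention code. OST and NEP effects are estimated separately and compared by an interaction test. The same section ties the primary outcome to mortality in the cohort as a whole. For the general-population analyses it says that "2013 to 2017 constitute the comparison period".

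**Power.** Power and sample size says: "Power was calculated based on potential mortality in these two groups (calculated conservatively for 4 years prior to the intervention". This gives 8000 comparison person-years against 3000 in the intervention period.

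**Entry to the cohort.** Patient eligibility requires adults to be "currently treated at the Addiction centres, or listed at NEP of Skåne County and have signed an informed consent". Under Recruitment, "Recruitment began in June 2018 and will end in June 2021", and "On completion of the training session, patients are asked if they are interested in participating in the study". The consent described there covers three years of register follow-up.

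**Those outside the cohort.** Data storage and missing data states: "There will be no registration of individuals declining naloxone training". Aggregated OST and NEP data will be used to describe whether participants differ from the wider groups. Trial status reports that, so far, "approximately 80% of patients are giving their consent to study inclusion" once training is complete.

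No section says who supplies the rows coded as comparison.

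**The concern.** A before/after rate ratio needs the same kind of person in both periods. Here the intervention period has a stated entry rule (alive, attending, trained, consenting) and the comparison period has none. The stated rule cannot be carried back, because consent began after the 2013–2017 period had ended. If the two periods are filled under different rules, the RR mixes any programme effect with the difference between clients who complete training and sign and clients in general. That affects the overall OST/NEP estimate, the two subgroup estimates and the interaction test. It matters more because this is the only comparison with a power calculation, and because Statistical methods links it to the primary outcome.

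**Working it through.** **1. The plan's own power figures.** Inputs from Power and sample size: n0 = 8000 and n1 = 3000 person-years, comparison rate p0 = 0.05 or 0.03, RR = 0.75 or 0.68, two-sided 5%. A two-proportion formula with pooled null variance was used:

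power = Φ[(p0 − p1 − 1.96·SE0)/SE1], where SE0 = √[p(1−p)(1/n0 + 1/n1)] with p the pooled rate, and SE1 = √[p0(1−p0)/n0 + p1(1−p1)/n1].

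- p0 = 0.05, RR 0.75: p1 = 0.0375, SE0 = 0.00451, SE1 = 0.00424, power 80.6% (stated 81%).
- p0 = 0.03, RR 0.68: p1 = 0.0204, SE0 = 0.00349, SE1 = 0.00321, power 80.4% (stated 81%).
- p0 = 0.03, RR 0.75: p1 = 0.0225, SE0 = 0.00353, SE1 = 0.00331, power 57.0% (stated 57%).

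The figures reproduce. They assume 8000 × 0.05 = 400 or 8000 × 0.03 = 240 comparison-period deaths. The calculation therefore presupposes comparison rows in which people can die.

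**2. Can the consent rule apply to those rows?** Consent runs from June 2018 to June 2021. A person who died in 2013–2017 cannot have signed, so none of the 240 to 400 deaths could belong to an eligible participant. The comparison rows must come from elsewhere, under a rule the article does not give. If the four years before the intervention are instead counted back from the 1 July 2019 start in Trial status, about the last year overlaps recruitment. Deaths among consented people in that year could then count, but those people had already been trained.

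**3. If consent applies to intervention rows only.** Suppose comparison rows are all clients, naloxone has no effect, 80% consent, and decliners die at k times the consenters' rate. Then

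spurious RR = 1/(0.8 + 0.2k).

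- k = 1.5: 1/1.1 = 0.91
- k = 2: 1/1.2 = 0.83
- k = 3: 1/1.4 = 0.71

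The 80% comes from Trial status; k is assumed. With k below 1 the RR would exceed 1.

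**4. Effect on the test.** Let consenters' mortality be s times that of all clients (s assumed), with no naloxone effect. Expected deaths are e0 = 8000·p0 and e1 = 3000·p0·s, and z = ln(s)/√(1/e0 + 1/e1). For s = 0.90 and p0 = 0.05, e0 = 400, e1 = 135 and z = −0.105/0.0995 = −1.06, which gives a 19% chance of p < 0.05. The chances for the values tried, against a nominal 5%:

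- s = 0.95: 8% at 50 per 1000, 7% at 30 per 1000
- s = 0.90: 19% and 13%
- s = 0.80: 57% and 38%

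**5. Passages side by side.** Statistical methods describes the open OST/NEP cohort as the one formed by those included, and ends person-time when a person leaves it. Recruitment continues register follow-up of consented patients for the full three years even after they stop attending. These are different cohorts, one defined by attendance and one by consent, and the text does not separate them.

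**The case against.** The strongest reply is that both periods are meant to use all OST and NEP clients found in records. The rows are coded by clinic type. The Methods subsection says NEP clients can be identified by personal number and their attendance followed over time. Data storage and missing data says statistical data come from registers. The consent rule would then govern only the prospective study of naloxone recipients, whose listed outcomes have no historical comparator. This reading is open and would remove the mismatch. It is not stated, however: the open cohort is introduced as that of the included participants, consent is its only entry rule, and the wider OST/NEP populations are mentioned only as aggregated data for description.

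Other parts of the reply stand in full:

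- The outcome listed under Primary outcome measures is opioid-intoxication mortality in the general population of Skåne. It does not depend on consent.
- A reader might infer that comparison rows are participants' own earlier years, with no deaths by construction. The documents do not support this. The power calculation assumes 30 to 50 deaths per 1000 comparison person-years, person-time starts at entry, and consent covers follow-up rather than past years.
- The 8000 person-years are partly a planning proxy, because the population at risk is unknown.
- The mortality ratios are assumed. Only the largest of the three gives an RR below 0.75. The 80% is an early report among people who completed training, not coverage of all clients.

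**Conclusion.** The point holds as an unreconciled definition that should be fixed. The article plans a before/after OST/NEP rate ratio, gives one cohort entry rule, and that rule cannot cover the comparison period. If it covers only the intervention period, selection by training and consent enters the RR, and age and sex adjustment does not remove it. The illustrated size is RR 0.91 to 0.71 with no true effect, against planned effects of 0.75 and 0.68. This rests on 80% consent and on assumed ratios of 1.5 to 3; the documents fix neither the size nor the direction.

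A reader might go further and conclude that the cohort RR is certainly biased, or that the trial's primary result is compromised. The documents do not support either conclusion: a record-based cohort in both periods remains possible, and the general-population comparison is untouched.

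**What to change.** Reconcile Power and sample size, Statistical methods and Patient eligibility as follows:

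- State that the before/after OST/NEP comparison, its subgroup analyses and the interaction test use all adults in OST or listed at NEP in each period, under one entry rule, regardless of training or consent.
- If individual linkage without consent is not approved, use aggregate deaths and person-years in both periods.
- Report consented participants, with the outcomes listed for included patients, only from the date of consent, with no rows coded as comparison and no before/after RR.

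The cost is mainly wording. An ethics amendment may be needed for register data on people who did not consent, and the before/after RR for consented participants is lost. If the sponsor already intends a record-based cohort in both periods, one sentence saying so is enough for the first item.
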